## 9 Adverse event reporting

### 9.1 Definition and Grading Intensity of Adverse Events (AE)

An AE is defined as any unintended change in the body structure (signs) or body function (symptoms), whether or not considered study-related. During confinement, subjects will be instructed to report all adverse events. All AEs, whether volunteered, elicited, or noted on physical examination, will be recorded throughout the study, eg, from the time of dose administration until study completion/discharge.

In addition, rating based on the National Cancer Institute (NCI) Common Toxicity Criteria (version 4.0, <http://ctep.cancer.gov/forms/CTCAEv4.pdf>), the AE intensity and changes over time will also be characterized as mild, moderate, severe, not related, possibly related, probably related, or definitely related based on the following definitions:

- Mild: Experience is minor and does not cause significant discomfort to subject or change to activities of daily living; subject is aware of symptoms but symptoms are easily tolerated.
- Moderate: Experience is an inconvenience or concern to the subject and causes interference with the activities of daily living.
- Severe: Experience significant interference with activities of daily living and the subject is incapacitated and/or unable to continue with activities of daily living.

### 9.2 Criteria for Determining Relationship to study procedures

The clinical investigator will make a determination of the relationship of the AE to the study procedures using a four-category system (not related, possibly related, probably related, definite).

Not related: Any untoward AE that either was clearly pre-existent, or occurred at the time of test procedures but sufficient information exists to indicate the etiology is unrelated to the clinical procedure.

Possibly related: An AE that does not follow a reasonable temporal sequence from the test procedure, does not follow a known or suspected response pattern, or could be explained by another etiology.

Probably related: An AE that follows a reasonable temporal sequence from the test procedure, follows a known or suspected pattern of response to the procedure, and cannot be reasonably explained by the known characteristics of the subject's clinical state.

Definitely related: An AE that follows a reasonable temporal sequence from test procedure and there is no other cause to explain the event, or a re-challenge (if feasible) is positive

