### 9.3 Serious adverse event

A serious Adverse Event (SAE) is any adverse event occurring at any dose that results in any of the following outcomes:

- Death;
- Life-threatening adverse experience;
- Inpatient hospitalization or prolongation of existing hospitalization;
- Persistent or significant disability/incapacity;
- Congenital anomaly/birth defect; and.
- Important medical events that may not result in death, be life-threatening, or require hospitalization may be considered a serious adverse event when, based upon the appropriate medical judgment, they may jeopardize the subject and may require medical or surgical intervention to prevent one of the outcomes listed in this definition.

Adverse events that fulfill criteria for Serious Adverse Event (SAE) will be reported to the sponsor within 24 hours of the known event and to the Institutional Review Board within 72 hours of the known event.

Hospitalizations for radiation therapy, should they occur, will not be considered as SAEs. Likewise, planned or elective procedures for pre-existing conditions (known prior to first administration of study drug) that are not related to a worsening of the condition after study drug initiation will not be considered as SAEs.

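### Section 9.2 makes lack of a temporal link sufficient for coding an adverse event possibly related, so attribution to study procedures is unreliable

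*Protocol*

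**What the plan says.** Section 9.2 asks the investigator to place every adverse event in one of four categories of relationship to the study procedures.

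- *Possibly related* is a list joined by a single *or*. Its first condition is "An AE that does not follow a reasonable temporal sequence from the test procedure", its second is the lack of a known or suspected pattern, and its last is that the event "could be explained by another etiology".
- *Not related* applies to an event that "either was clearly pre-existent, or occurred at the time of test procedures but sufficient information exists to indicate the etiology is unrelated" to the procedure.
- *Probably related* begins "An AE that follows a reasonable temporal sequence from the test procedure, follows a known or suspected pattern of response to the procedure" and adds that the subject's clinical state does not reasonably account for the event.
- *Definitely related* needs the timing link and no other cause, or a positive re-challenge.

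On recording, Section 9.1 says that adverse events "will be recorded throughout the study, eg, from the time of dose administration until study completion/discharge". It also speaks of confinement. Section 9.3 defines an SAE by reference to any dose. Its exception for planned or elective procedures is limited to conditions "known prior to first administration of study drug".

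The study itself is observational. Under Section 4.1 participation begins at informed consent. Section 9.4.1.4 states that radiation is standard of care and not an experimental part of the protocol, and it names six short-term radiation effects: fatigue, skin erythema, desquamation, breast edema, breast tenderness and myositis.

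**The concern.** A causality scale should run from no link to a firm link. Here the second step is entered by failing the test of timing, which is normally the main reason to call an event unrelated. The first step is too narrow to take those events back.

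What is at stake is the summary of events attributed to study procedures. The protocol has reasons to want that summary to be right. Section 9.4.3 calls the benefit-risk balance mildly negative, partly because of possible pain from ultrasound. Section 9.4.1.4 says that reporting radiation effects may matter, because their influence on model accuracy is unknown. Section 6.8.1 schedules radiation at weeks 1, 3 and 6, the same weeks as the first three ultrasounds, so the investigator will often have to separate the two sources. Two investigators applying the text faithfully could code the same event differently.

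A lesser matter is that Sections 9.1 and 9.3 refer to a dose and a study drug that this study does not have.

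**Working it through.** There is no figure in the plan to reproduce. The check is a reading of the four definitions against each other.

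**Inputs.** Three yes/no features, all from Section 9.2: T, a reasonable temporal sequence from the procedure; P, a known or suspected response pattern; E, another explanation exists. One assumption is needed: the other etiology in *possibly related* and the subject's clinical state in *probably related* are treated as the same feature E. Re-challenge is left out.

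**Definitions as logic.**
- Possibly, with *or* as written: (not T) or (not P) or E
- Possibly, if the list were meant as *and*: (not T) and (not P) and E
- Probably: T and P and (not E)
- Definitely: T and (not E)

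| T | P | E | Possibly (or) | Possibly (and) | Probably | Definitely |
|---|---|---|---|---|---|---|
| yes | yes | yes | x | | | |
| yes | yes | no | | | x | x |
| yes | no | yes | x | | | |
| yes | no | no | x | | | x |
| no | yes | yes | x | | | |
| no | yes | no | x | | | |
| no | no | yes | x | x | | |
| no | no | no | x | | | |

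**Result with *or*.** *Possibly related* holds in 7 of 8 profiles and is the exact complement of *probably related*. It includes all 4 profiles without a temporal link. The profile with a temporal link, no known pattern and no other cause meets both *possibly* and *definitely related*.

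**Result with *and*.** *Possibly related* shrinks to 1 of 8 profiles and still requires that the temporal link be absent. *Definitely* takes 2 profiles, one of which is also *probably*, so 8 − 1 − 2 = 5 profiles have no category unless the separate wording of *not related* happens to apply. The conjunctive reading therefore does not rescue the definition.

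**Can *not related* take the unlinked events?** It has two routes: the event was pre-existent, or it occurred at the time of a procedure and its unrelated cause is established. A new event between visits, without a temporal link to any procedure, meets neither. Under the text as punctuated it can only be *possibly related*.

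**Overlap.** Take breast tenderness from radiation, present at an ultrasound visit. If the information is sufficient to show that the cause is radiation, it meets the second route of *not related*. It also has another etiology, so it meets *possibly related*. The text gives no order of precedence.

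**Start of recording.** The rule in Section 9.1 is recording throughout the study, and the dose appears only as an example of the start. Section 4.1 supplies a start, namely consent, which under Section 6.8.2 may come up to 21 days before surgery. The example is unsuitable, but the rule stands. The SAE exception in Section 9.3 has no such general rule behind it: its cut-off is tied to an event that does not occur in this study.

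**The case against.** The strongest reply is that nothing in the protocol acts on the relatedness code. Events are recorded whether or not they are thought study-related. SAEs go to the sponsor within 24 hours and to the IRB within 72 hours with no relatedness condition. No withdrawal or discontinuation rule in Section 8 uses causality. Ultrasound burden is measured separately by pain scores before and after the scan. All of this is correct and limits the consequence to the coding itself. It does not make the coding right: Section 9.2 requires the determination, and following its rule gives wrong attributions.

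A second reply is that investigators will use judgment. That may soften the effect of the overlap, but it does not give an unlinked new event a place in *not related*.

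Three stronger readings might be inferred, and the protocol does not support them.

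- *The adverse event window never opens, or opens only at the first radiation dose.* Recording is required throughout the study, the dose is only an example, participation starts at consent, and Section 9.4.1.4 excludes radiation as a study intervention. A loss of early events does not follow.
- *Most adverse events in the 12 to 15 subjects would be coded possibly related.* The protocol gives neither event rates nor timing, and radiation effects seen at a visit can also meet *not related*. All that can be said is that each of the six named short-term effects can meet the *possibly related* wording.
- *Possibly related is defined solely by the absence of a temporal link.* That absence is one of three alternatives, although as written it is enough on its own.

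**Conclusion.** The point holds for Section 9.2. As written, a new adverse event without a temporal link to any study procedure is coded *possibly related*, and an event at a procedure with a known other cause fits two categories. The count of 7 of 8 profiles depends on treating the two phrases about another explanation as one feature. The finding about unlinked events does not depend on that, since it follows from the first condition and the narrow scope of *not related*.

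The size in events or subjects cannot be derived from the protocol. The effect is confined to procedure-relatedness coding; the primary endpoint, its 60% criterion, the sample size and the SAE reporting clocks are untouched. It is worth correcting because the rule is wrong on its face and cheap to repair. The drug-trial wording in Sections 9.1 and 9.3 is secondary.

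**What to change.** In Section 9.2, change two definitions.

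- *Possibly related*: the event follows the study procedure in a reasonable temporal sequence but could also be explained by another cause.
- *Not related*: keep the pre-existent route, and extend the category to events without a reasonable temporal sequence from a study procedure and to events with a clearly established other cause, whenever they occur.

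All 4 profiles without a temporal link then fall under *not related*. An event with a temporal link and another explanation is *possibly related* unless that other cause is clearly established. The boundary between *probably* and *definitely related*, which share one profile in the table, can be tidied in the same edit.

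As a clean-up, reconcile with the observational design and the start of participation in Section 4.1: the references to confinement and dose administration in Section 9.1, and in Section 9.3 the reference to any dose and the two references to study drug that set the cut-off for planned procedures.

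The cost is about seven wording edits in Section 9 (2 in Section 9.2, 2 in Section 9.1, 3 in Section 9.3), with the IRB approval that Section 10.2 requires for any protocol change. Visits, procedures and care do not change. Any events already coded would need their relatedness reviewed once.

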### 9.3 Serious adverse event

A serious Adverse Event (SAE) is any adverse event occurring at any dose that results in any of the following outcomes:

- Death;
- Life-threatening adverse experience;
- Inpatient hospitalization or prolongation of existing hospitalization;
- Persistent or significant disability/incapacity;
- Congenital anomaly/birth defect; and.
- Important medical events that may not result in death, be life-threatening, or require hospitalization may be considered a serious adverse event when, based upon the appropriate medical judgment, they may jeopardize the subject and may require medical or surgical intervention to prevent one of the outcomes listed in this definition.

Adverse events that fulfill criteria for Serious Adverse Event (SAE) will be reported to the sponsor within 24 hours of the known event and to the Institutional Review Board within 72 hours of the known event.

Hospitalizations for radiation therapy, should they occur, will not be considered as SAEs. Likewise, planned or elective procedures for pre-existing conditions (known prior to first administration of study drug) that are not related to a worsening of the condition after study drug initiation will not be considered as SAEs.

### 9.4 Potential risks and discomforts

#### 9.4.1 Risks

##### 9.4.1.1 3-Dimensional Camera Imaging

There are no risks associated with the 3-dimensional 180° camera surface imaging. The camera will not be in contact with the subject's skin.

##### 9.4.1.2 Ultrasound

There are no known long-term side effects of ultrasound. The ultrasound procedure is not expected to cause discomfort to the patient but pain will be assessed/quantified pre/post ultrasound at each visit in order to capture this information. If at any time the subject expresses the desire to discontinue the ultrasound procedure, they will be allowed to discontinue the procedure.

#### 9.4.1.3 Thermal imaging

There are no risks associated with the thermal imaging camera. The camera will not be in contact with the subject's skin.

#### 9.4.1.4 Risks associated with radiation therapy

Radiation therapy risks are noted as part of the protocol, but radiation procedures are not an experimental component of this protocol; they are standard of care for BCT. Long-term effects include radiation pneumonitis, rib fractures, and (if the left breast is the side to receive radiation) cardiac complications. Short-term side effects of radiation therapy include fatigue, skin erythema, desquamation, breast edema, breast tenderness and myositis. Reporting of radiation therapy side effects may be important in this study because we do not know how they will impact the accuracy of the multiscale model.

#### 9.4.2 Potential benefits

This study will improve the knowledge of clinicians who perform BCT. It will provide needed information for improving the BCT procedure if the multiscale model is successful. But subjects participating in this pilot study will not benefit directly from this research.

#### 9.4.3 Risk:Benefit ratio

The benefit:risk for participants in this study is considered mildly negative given that the subject is not expected to benefit directly from the research and might experience mild pain during the ultrasound procedures. Participating in the study may be perceived as an inconvenience to some patients.

## 10 Ethics

### 10.1 Responsibilities of the investigator

The Principal Investigator will maintain complete study files (electronic and/or paper) to enable full documentation of the study procedures and data for purpose of verification and study analysis.

The Principal Investigator, or her designee, will explain the nature of the study to the subject, inform the subject that participation is voluntary and that withdrawal at any time is allowed. The Principal Investigator will maintain documentation of written informed consent.

This study will be conducted using Good Clinical Practice as identified by

- International Conference on Harmonization (ICH) Tripartite Guidelines for Good Clinical Practice
- US Code of Federal Regulation (CFR) dealing with clinical studies (21 CFR parts 50, 54, 56 and 312)
- The principles stated in the Declaration of Helsinki concerning medical research in humans

### 10.2 Institutional review board approval

This study will be reviewed and approved by The Methodist Hospital Research Institute Institutional Review Board (TMHRI IRB) prior to commencement of any subject-specific activities. A current letter of IRB approval will be maintained with the study files. No changes to

the protocol or informed consent form will be made prior to or without documented approval from TMHRI IRB.

All subjects will provide consent (indicated by their signature or their legally authorized representative's signature on the approved Informed Consent Form) prior to initiation of any study-related activities. Signed and dated ICFs will be maintained with the study archives.

## **11 Data handling and recordkeeping**

### **11.1 Confidentiality**

In order to maintain confidentiality, the subject will be identified only by his/her study screening number and/or randomization number.

### **11.2 Flow of information and records to be kept**

Throughout the conduct of this study, all required data will be recorded in electronic CRFs that have been specifically designed to record all observations and other data pertinent to this clinical investigation. Data reported on CRFs should be consistent with source documents when applicable, or the discrepancies should be explained. Any change or correction to a CRF will produce an audit trail within the electronic CRF system and will identify the user, date and time of the change.

The CRFs should be completed in a timely fashion. The complete electronic CRFs will be maintained by the study site, as is required by institutional, local and government regulations.

The clinical investigator is responsible for maintaining adequate and accurate records as specified in Essential Documents for the Conduct of a Clinical Trial (section 8 of the ICH Guideline for Good Clinical Practice) to enable the conduct of the study to be fully documented and the study data to be subsequently verified.

Upon study termination, original documents will be maintained at TMHRI.

## **12 Financing**

Funding for this study is provided by The Methodist Hospital Department of Surgery.

## **13 Publication policy**

The Principal Investigator holds final approving authority over whether or not any proposed publication (eg, abstract, manuscript) based on the data generated from this study can or should be submitted for publication to journals, scientific meetings, or any other medium.

## 16 Appendices

### 16.1 Informed Consent Form

## 16.2 Pain Scale Score

Subject Initials: \_\_\_\_\_ Date: \_\_\_\_\_ Visit: \_\_\_\_\_ Pre or Post (circle) Ultrasound

### 0-10 Numeric Pain Intensity Scale\*

[figure not shown]

\*If used as a graphic rating scale, a 10-cm baseline is recommended.

From: Acute Pain Management: Operative or Medical Procedures and Trauma, Clinical Practice Guideline No. 1. AHCPR Publication No. 92-0032; February 1992. Agency for Healthcare Research & Quality, Rockville, MD; pages 116-117.

A7012-AS-2

### 16.3 Harvard/NSABP/RTOG scale score

The Harvard/NSABP/RTOG scale score is a 4-point scale of breast cosmesis, which will be assessed by clinicians at baseline (after surgery) and two additional times during follow-up (week 10 and week 26).

#### **Harvard/National Surgical Breast and Bowel Project/Radiation Therapy Oncology Group Breast Cosmesis Grading Scale**

“I. Excellent: When compared with the untreated breast, there is minimal or no difference in the size or shape of the treated breast. The way the breasts feel (its texture) is the same or slightly different. There may be thickening, scar tissue, or fluid accumulation within the breast but not enough to change the appearance.

“II. Good: There is a slight difference in the size or shape of the treated breast as compared with the opposite breast or the original appearance of the treated breast. There may be some mild reddening or darkening of the breast. The thickening or scar tissue within the breast causes only a mild change in the shape or size.

“III. Fair: Obvious difference in the size and shape of the treated breast. This change involves one-quarter or less of the breast. There can be moderate thickening or scar tissue of the skin and the breast, and there may be obvious color changes.

“IV. Poor: Marked change in the appearance of the treated breast involving more than one-quarter of the breast tissue. The skin changes may be obvious and detract from the appearance of the breast. Severe scarring and thickening of the breast, which clearly alter the appearance of the breast, may be found.”
